### 2.5. Interventions

There were 2 phases in this study. Once the patients finished hysteroscopic adhesiolysis, they would accept treatment according to the dividing of each group for 2 menstrual cycles. After the first phase of treatment, operative hysteroscopy would be carried out for all of these patients to evaluate restoring the uterine cavity. Patients will be treated for one menstrual cycle during the second phase, depending on the group. Moreover, we then conducted a logical image examination of other outcomes after that.

#### 2.5.1. Treatment group.

The patients in the treatment group will receive electrical stimulation combined with ultrasound acupuncture and oral hormone supplementation for 3 menstrual cycles. Treatment would begin on the day the patient underwent hysteroscopic adhesiolysis. Estrogen progestogen sequential therapy is as follows: during the menstrual cycle of hysteroscopic adhesiolysis, on day 2 after hysteroscopic adhesion release, oral estradiol valerate 2 mg (Progynova; Schering, Weesp, The Netherlands) was administered twice daily for 21 days; from day 10, oral dydrogesterone 10 mg twice daily for 10 days. Those with menstruation began to take the next cycle on the fifth day of menstruation, and those without menstruation began to take the next cycle after 7 days of drug withdrawal. Three consecutive menstrual cycles would be taken.

Electrical stimulation combined with ultrasound acupuncture therapy is as follows: the device is called ULTRA-EMS THERAPY DEVICE MLD C7000 (Nanjing Medlander Medical Technology Co. Ltd, Nanjing, China). During the menstrual cycle, Patients would be treated with TENS and ultrasound acupuncture modalities for 7 days from the first day after the patient undergoes hysteroscopic adhesion release. Each patient visit lasted approximately 30 minutes. TENS includes 8 electrode pads, which correspond to different body positions, as shown in the figure below. Table 1 shows the TNES and acupuncture points. The electrode piece used for TENS is a body surface electrode-circular 50 mm (viscose electrode piece), which is reusable and specially used by specially assigned persons. It is discarded after ten times of use. Stimulation current intensity is as follows:: adjustable within the range of 0 to 100 mA, adjustable with the step of 0.5 mA. Intensity adjustment is based on the patient’s tolerance to the degree that the patient can feel the current stimulation. When the patients accept TENS, the doctors put electrode pieces on the surface of the body (S1-8). The ultrasound acupuncture includes a therapeutic ultrasound probe and ultrasonic therapy fixing paste. Therapy fixing paste is used for applying an ultrasonic probe to acupoints on the body surface (A1-8). The ultrasound acupuncture mode has 10 shifts with adjustable and effective sound intensity: less than 3 W/cm^2^. Typically, we used the sixth shift for patients. During the 2 to 3 menstrual cycle, TENS, ultrasound acupuncture, and intermittent vaginal electrical stimulation would be used for patients from 5 to 7 days of the menstrual cycle. TENS and ultrasound acupuncture are the same as the first menstrual cycle. Intermittent vaginal electrical stimulation is as follows: all women had their own vaginal probe (Nanjing Medlander Medical Technology Co. Ltd, Nanjing, China, MLD CV01). Doctors applied ointment (conductive gel) to the probe tip prior to insertion into the vagina and inserted the stylet approximately 6 to 8 cm deep. An adhesive electrode will be placed on the skin outside the vagina (on the female thigh). The vaginal probe will be left in the vagina, and electrical stimulation was started. The selected parameters included a biphasic intermittent biphasic current with a frequency of 40 Hz, a pulse width of 250 us, and a current intensity between 0 and 120 mA. On-off (duty cycle) periods were individually adjusted based on each female’s ability to maintain voluntary contractions. TENS, ultrasound acupuncture, and intermittent vaginal electrical stimulation would last about 30 minutes every time.

**Table 1 T1:** Description of transcutaneous electrical nerve stimulation and acupuncture points.

**Stimulation type**	**Name**	**Localization**	**Point**
TENS	S1	Left external iliac artery, left groin	NA
TENS	S2	Right external iliac artery, right groin	NA
TENS	S3	Left femoral surface projection area, left gastrocnemius surface projection area	NA
TENS	S4	Right femoral surface projection area, right gastrocnemius surface projection area	NA
TENS	S5	Pelvic surface projection area, dorsal penetration (upper left)	NA
TENS	S6	Pelvic surface projection area, dorsal penetration (left lower)	NA
TENS	S7	Pelvic surface projection area, dorsal penetration (upper right)	NA
TENS	S8	Pelvic surface projection area, dorsal penetration (right lower)	NA
Ultrasound acupuncture	A1(left), a2(right)	In the flat umbilicus, 2 inches from the umbilicus, the width of the navel to the left and right 3 fingers	Tianshu
Ultrasound acupuncture	A3(left), a4(right)	The patient was placed in the decubitus position, 4 inches below the umbilicus (5 finger widths) and 3 inches aside (4 finger widths)	Zigong
Ultrasound acupuncture	B1(left), b2(right)	Calf nose (sitting or supine position, when the lower limbs are strongly pushed straight, located in the depression below the rubber cover, generally known as “external knee eye”) 3 inches below (4 finger width)	Zusanli
Ultrasound acupuncture	B3(left), b4(right)	Located on the medial side of the lower leg, 3 inches above the medial malleolus (4 finger width)	Sanyinjiao

NA= not available, TENS = transcutaneous electrical nerve stimulation.

####  Control group.

2.5.2.

The control group received oral hormone supplementation for 3 menstrual cycles. The protocol was the same with oral hormone supplementation in the treatment group.

### 2.6. Outcome measures

#### 2.6.1. Primary outcome.

a) Improvement of IUAs

The primary outcome of our study was the clinical response rate. After 2 menstrual cycles of treatment (about 2 months), hysteroscopy was performed to evaluate the recovery of endometrial cavity function. According to the recovery status, the clinical outcomes were classified into 3 levels (cure, improvement, and failure). These 3 stages had different standards. The first is the cure: after intrauterine treatment, the size and shape of the uterine cavity were normal, and the uterine angle and tubal opening were normal. The second is the improvement: IUAs score decreased after treatment. The severity of adhesions according to the American Fertility Society (AFS) IUA 19 classification.^[20]^ The last is the failure: they were unchanged clinical symptoms and a massive IUA condition. Overall response rate = (cure + improvement)/total number of cases *100%.

b)IUA evaluations

Before treatment, we evaluated and scored the severity of adhesions according to the American Fertility Society (AFS) IUA 19 classification.^[20]^ One of 2 reproductive surgeons in our hospital performed all operative hysteroscopies using the same techniques. During the operative hysteroscopy, the doctors then did hysteroscopic adhesiolysis for patients. Scores of 1 to 4 represent mild adhesions, 5 to 8 points for moderate adhesions, and 9 to 12 points for severe adhesions. Table 2 shows the details of the evaluation of IUA.

**Table 2 T2:** Score assessment of intrauterine adhesion.

**Evaluation variable**	**Score**

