## 1. Introduction

Intrauterine adhesions (IUAs) were first reported by Fritsch in 1894.^[1]^ In 1950, Asherman systematically and comprehensively reported IUA through a summary of 29 IUA cases, so that people began to pay attention to and deeply studied this disease. Also, the IUAs is also known as Asherman syndrome.^[2]^ It is characterized by varying degrees of scar formation in the uterine cavity and is also the cause of menstrual disorders, infertility, and placental abnormalities.^[3,4]^ IUA occurs most often after infection or trauma, such as uterine surgery, especially in the postpartum period of cesarean section.^[5,6]^ A large number of inflammatory chemokines, together with cytokines and cell adhesion molecules, are aberrantly expressed during the development of IUA.^[7]^ The current report found that IUA was associated with decline in reproductive clinical outcomes after natural conception and assisted reproductive technologies.^[8]^ The prevalence of IUAs is currently not entirely consistent, ranging from 0.3% (an incidental finding in women with intrauterine device placement without gynecological symptoms) to 21.5% (women with postpartum curettage).^[9]^ Of all the tools used to diagnose IUA or evaluate the severity of IUA, hysteroscopy is the current gold.^[10]^ In the treatment, the recovery of uterine shape and function is mainly helped by surgical separation of the adherent uterine cavity, supplemented by physical isolation and hormone to promote endometrial regeneration.^[8]^ Operative hysteroscopy is also considered a good treatment for patients.^[11]^ The postoperative effectiveness of hysteroscopic separation of IUAs is generally satisfactory, and the probability of usual or improved menstruation after surgery can reach 92% to 96%.^[12]^ Recurrence of postoperative adhesions is one of the most important factors for poor reproductive outcome after operative hysteroscopy, especially in cases diagnosed with severe AS, where the recurrence rate is significantly higher.^[13]^ More and more scholars have focused on exploring the measures to prevent adhesion recurrence and improve postoperative pregnancy rate during and after operative hysteroscopy.^[10]^

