Electrical stimulation, including Neuromuscular Electrical Stimulation (NMES) and transcutaneous electrical nerve stimulation (TENS), has been applied in the treatment of stress urinary incontinence, pelvic pain, and sexual dysfunction.^[14]^ Some researchers also did a preliminary study of NMES in reproductive medicine and have improved the clinical pregnancy rate.^[15]^ The mechanism of action in NMES and TENS is related to the mechanism of recurrence of IUAs. Acupuncture has many applications in treating various reproductive disorders, such as polycystic ovary syndrome, pain induced by oocyte retrieval, diminished ovarian reserve, embryo transfer, and oligospermia/asthenospermia.^[16–18]^ Some observational studies have evaluated the effectiveness of prevention of recurrence of IUAs.^[19]^ The electrical muscle stimulation combined with ultrasound acupuncture (ULTRA-EMS) therapy device C7000 (Nanjing Medlander Medical Technology Co. Ltd, Nanjing, China), combined TENS, NMES, and ultrasound acupuncture and has been used for reproductive medicine. Nevertheless, this combination has not been evaluated for the treatment or prevention of recurrence of IUAs after operative hysteroscopy.

This study aims to evaluate the effectiveness of ULTRA-EMS in preventing the recurrence of IUAs after operative hysteroscopy.

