### 2.9. Statistical considerations

#### 2.9.1. Sample size estimation.

The number of patients required for this trial was determined on the basis of the primary outcome of the clinical response rate. With an estimated clinical response rate of 56.6% in the control group, we calculated that 168 participants would be required for the trial to achieve 80% power (β = 0.2) to detect a 20% difference in a clinical response rate increase in the trial groups. The allocation ratio was 1:1, at a 2-sided overall significance level of 5% (α = 0.05). The test statistic used was the 2-sided Z-Test with unpooled variance. With an estimated follow-up loss of 20%, we aimed to recruit 105 participants per group, which was 210 participants in total.

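### The primary response rate pools cure with any fall in the AFS total, so a positive result would not show that adhesion recurrence, the stated aim, was prevented

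*Protocol article*

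**What the plan says.** **Aim.** The Introduction states: "This study aims to evaluate the effectiveness of ULTRA-EMS in preventing the recurrence of IUAs after operative hysteroscopy". Section 2.1 repeats this and adds reproductive outcomes; the Discussion again names recurrence.

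**Primary outcome.** Section 2.6.1 grades the second-look hysteroscopy, after two treated cycles, as cure, improvement or failure. Cure requires a normal cavity, uterine angle and tubal opening. For improvement: "The second is the improvement: IUAs score decreased after treatment". Failure is described as unchanged symptoms together with massive adhesions. The response rate is cure plus improvement over all cases.

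**Reference score.** Section 2.6.1 b) says: "Before treatment, we evaluated and scored the severity of adhesions according to the American Fertility Society (AFS) IUA 19 classification", and then: "During the operative hysteroscopy, the doctors then did hysteroscopic adhesiolysis for patients". Section 2.5 applies to all patients: "Once the patients finished hysteroscopic adhesiolysis, they would accept treatment according to the dividing of each group for 2 menstrual cycles". Section 2.5.1 adds: "Treatment would begin on the day the patient underwent hysteroscopic adhesiolysis". No score after adhesiolysis is described as a reference.

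**Score.** Table 2 adds extent (1, 2, 4), type (1, 2, 4) and menstrual pattern (0, 2, 4).

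**Other outcomes.** The secondary outcomes in section 2.6 are menstrual blood loss, three-dimensional ultrasound, and pregnancy. None counts adhesion recurrence.

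**The concern.** Recurrence after adhesiolysis means that adhesions are present again in a cavity that surgery had opened. The improvement level asks something else: whether the total is lower than it was, apparently, before surgery. A woman can have recurrence and still be counted as a success, provided that the adhesions came back to a lesser degree or that her bleeding improved.

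What is at stake is the conclusion. If the response rate is higher in the treatment group, the report will be tempted to say that the device prevents recurrence. The pooled rate cannot carry that statement, because its numerator includes women whose adhesions have recurred.

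**Working it through.** **1. The plan's own sample size.** Inputs from section 2.9.1: 56.6% v 76.6%, two-sided 5%, 80% power, unpooled Z-test, 20% loss.

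n per arm = (1.960 + 0.842)² × (0.566×0.434 + 0.766×0.234) / 0.20² = 7.849 × 0.4249 / 0.04 = 83.4, so 84 per arm and 168 in all. With loss: 84 / 0.80 = 105 per arm, 210 in all. Both figures reproduce. The point is what the outcome measures, not this arithmetic.

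**2. Reference time.** The definition of improvement names none. Treatment starts on the day of adhesiolysis, the score is taken before treatment, and the adhesiolysis follows the scoring. The pre-adhesiolysis score is thus the only candidate in the text. This is an inference, though a strong one.

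**3. What the rule permits (Table 2, extent + type + menses).**

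| Before surgery | Second look | Adhesion items | Class by the score rule |
|---|---|---|---|
| 2+2+2 = 6 | 2+1+2 = 5 | adhesions back over the same extent, milder type | improvement |
| 4+4+2 = 10 | 4+4+0 = 8 | identical | improvement |
| 1+1+2 = 4 | 1+2+0 = 3 | worse (filmy to filmy + dense) | improvement |

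All three start from hypomenorrhea, which a regular cycle at entry (section 2.3) does not exclude.

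**4. How many patterns.** With adhesions present at both times there are 3×3×3 = 27 patterns and 27×27 = 729 before/after pairs. By enumeration, 321 have a lower total. Those in which neither extent nor type is better than before can be counted by hand. The loss of menstrual points must exceed the rise in extent + type. For one item, 3 transitions leave the score unchanged and 1 each raises it by 1 (1→2), 2 (2→4) or 3 (1→4).

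- Menses fall by 2: the rise must be 0 or 1, so 3×3 + 2×(3×1) = 15 pairs. This arises twice (2→0 and 4→2): 30.
- Menses fall by 4: the rise must be at most 3, so 3×6 + 1×5 + 1×4 + 1×3 = 30 pairs.
- Total: 30 + 30 = 60 of 321.

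If the regular-cycle criterion makes baseline amenorrhea ineligible, only 2→0 remains: 15, out of 155 pairs with a lower total. These are possible patterns, each counted once. They are not patient frequencies.

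**5. Aim against outcome.** Cure requires a normal cavity, so it bears on recurrence. Improvement does not, and the primary rate adds the two.

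**The case against.** **The response rate suits a treatment trial.** The title and section 2.2 speak of treating adhesions, and a graded response on the AFS scale fits that wording. This stands, so the response rate need not be replaced. It does not remove the gap: recurrence is the aim in the Introduction, section 2.1 and the Discussion, and no named outcome counts it.

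**The cure level already measures recurrence.** In part it does, and to say that the trial collects nothing on recurrence would be too strong. But cure is analysed only as a component of the pooled rate.

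**The worked example might be a failure.** Unchanged dense adhesions over more than two thirds of the cavity could be called massive. But failure as written also asks for unchanged symptoms, and hers have changed. The text does not clearly place her in either class.

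**Surgery is common to both arms.** Correct. The shared credit does not by itself favour an arm.

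**A tempting stronger reading is that the trial is underpowered.** A reader might note that the Introduction says "the probability of usual or improved menstruation after surgery can reach 92% to 96" per cent, infer that the control rate will be near its ceiling, and set this against "With an estimated clinical response rate of 56.6% in the control group". The document does not support this. The 56.6% bears the same name as the primary outcome and may already include the credit for surgery; no source is stated against which to check it. The menstrual figure is an upper reach for usual or improved bleeding and may include women who were normal before, so it is not a rate of falling scores. Nor does a higher control rate alone cost power: at 84 per arm, 80% v 95% gives (0.15 − 1.96×0.0510)/0.0497 = 1.01 with the pooled test, that is 84% power. Low power follows only if a smaller difference is assumed as well.

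**Conclusion.** The concern holds as a mismatch between the aim and the primary outcome. As written, a higher response rate would not show that recurrence was prevented, because women with re-formed adhesions, or with unchanged adhesions and better bleeding, can be responders in either arm.

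Its size in patients cannot be given. The document has no recurrence rate and no distribution of baseline scores; the pattern counts (60 of 321, or 15 of 155 without baseline amenorrhea) show only that the rule allows such cases. No bias towards one arm and no shortfall in power follows from this point. The verdict rests on one inference, that the reference is the pre-adhesiolysis score. The menstrual part would remain under any reference score that includes menses.

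**What to change.** 1. Name adhesion recurrence at the planned second-look hysteroscopy (any adhesion present, yes/no) as a key secondary outcome, with the between-arm difference and its 95% confidence interval.
2. Report cure separately from improvement, and rest any conclusion on recurrence on items 1 and 2, not on the pooled rate.
3. State in section 2.6.1 that the reference for improvement is the pre-adhesiolysis score.
4. Add a sensitivity analysis of response on extent + type only, so that a change in menses alone cannot make a responder. This still credits adhesiolysis in both arms and so does not replace item 1.
5. Ask the sponsor to confirm that the 56.6% was obtained under the response definition of section 2.6.1.

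**Cost.** The primary outcome and the sample size stay as they are, and no visit is added, because the hysteroscopy is already planned. Protocol and registry wording must change, before the arms are compared. The added outcome may look less favourable than the pooled rate. It also cannot tell re-formed adhesions from incompletely divided ones, since no post-adhesiolysis score is described. No power can be stated for it, but its precision can be bounded: with 84 per arm, the half-width of the simple 95% interval for the difference is at most 1.96 × √(2×0.25/84) = 0.151, about 15 percentage points.

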**Extent of cavity involved**	
<1/3	1
1/3–2/3	2
>2/3	4
**Type of adhesions**	
Filmy	1
Filmy + dense	2
Dens	4
**Menstrual pattern**	
Normal	0
Hypomenorrhea	2
Amenorrhea	4

#### 2.6..2. Secondary outcomes.

a)Menstruation outcome

We assessed the amount of menstrual status according to Higham’s pictorial blood loss assessment chart.^[21]^ Methods: 240 mm sanitary napkins were uniformly used, and the blood penetration area of each piece of switched sanitary napkins was recorded. Mild: blood penetration area ≤ 1/3 of 1 point of the total area of the sanitary napkin. Moderate: the blood penetration area accounts for 1/3 to 3/5 of the 5 points of the entire sanitary napkin area. Severe: the bleeding area is basically 20 points of the entire sanitary napkin area. The size of the lost blood clot is 1 point for small blood clots < 1 coin; 5 points for large blood clots ≥ 1 coin. When blood clots could not represent blood loss, the percentage of the recorded blood volume was estimated for recording. The score, quantity and days of each sanitary napkin were filled in the sanitary napkin count and score table. Table 3 shows the menstrual blood loss record card. Menstrual blood loss score = (number of sanitary napkins with a large amount of blood-stained × 20) + (number of sanitary napkins with a medium amount of blood-stained × 5) + (number of sanitary napkins with a small amount of blood-stained × 1) + (number of blood clots < 1 coin × 1) + (blood clots ≥ 1 coin × 5). We recorded the menstrual status before and after 2 menstrual cycles of treatment.

**Table 3 T3:** Record card for menstrual blood loss and assessment time point.

	**Menstrual cycle**						
**Blood staining level of sanitary napkin**	**1st day**	**2nd day**	**3rd day**	**4th day**	**5th day**	**6th day**	**7th day**
Severe							
Moderate							
Mild							
Blood clots < 1 coin							
Blood clots ≥ 1 coin							
Menstrual color							
Dysmenorrhea							

b)*Changes in 3-dimensional vaginal ultrasonography*

The changes in endometrial structure and hemodynamics before and after treatment will be evaluated in both groups. Vaginal 3-dimensional ultrasonography was performed by the same physician (attending and above grade) during ovulation before treatment (12 to 14 days before menstruation) and ovulation after the third course of treatment, mainly measuring endometrial type, endometrial thickness (ED), endometrial volume, endometrial classification (A, B, C), uterine artery blood flow (PI, RI, S/D, PS), endometrial vascular index (VI), blood flow index (FI), vascular blood flow index (VFI), and blood flow classification (I, II, and III).

c) *Pregnancy rates and pregnancy outcomes*

Pregnancy rate and pregnancy outcome would be follow-up at 2 and 6 months after operation in both groups. The purpose of the follow-up was to evaluate the long-term effectiveness of the electro-ultrasound device intreating IUAs. Researchers will pay close attention to the patient’s pregnancy during the follow-up period.

### 2.7. Withdrawn

The reason for participants who withdrew would be recorded for the withdrawn (e.g., adverse event, lack of effectiveness).

### 2.8. Study timeline

The study is expected to take 12 months to complete data collection, including 7 times of data collection. According to SPIRIT,^[22]^ the schedule of interventions and assessments is shown in Figure 1. The flow chart of enrollment of study participants was shown in Figure 2.

